## Abstract

**Background:**

We have argued against the traditional approach of counselling avoidance of all triggers of headaches and migraine. Problems with this approach include the impossibility of avoiding all triggers and the high costs associated with trying to do so, and that avoidance could lead to reduced tolerance for the triggers. We have developed an alternative approach called *Learning to Cope with Triggers* (LCT) that encourages avoidance of triggers that are detrimental to health and wellbeing, but uses exposure to other triggers to desensitise headache sufferers to the triggers. This approach has been shown to be more effective than advising avoidance of all triggers. Trigger management is only one component of a comprehensive treatment program and the current study is designed to evaluate a new approach to treating headaches in which LCT has been integrated into an established cognitive-behavioural therapy (CBT) package (LCT/CBT).

**Methods/Design:**

A target sample of 120 adult participants who suffer from migraine or tension-type headache, at least six days per month, and have done so for at least 12 months will be recruited. Participants will be randomly assigned to one of three groups: LCT/CBT; Avoid/CBT (CBT combined with instructions to avoid all triggers); and waiting-list control. Measures will include: daily diaries for recording headaches, triggers and medication consumption; headache disability and quality of life; trigger avoidance; locus of control and self-efficacy; and coping strategies. Treatment will involve 12 60-minute sessions scheduled weekly. Assessment will be completed before and after treatment, and at 4 and 12 month follow-up. The data will be analysed to determine which approach is most effective, and predictors of response to treatment.

**Discussion:**

Migraine and tension-type headache are common and can be disabling. CBT has been demonstrated to be an efficacious treatment for both disorders. However, there is room for improvement. This study aims to increase the efficacy of behavioural approaches and identify factors predictive of a positive response.

**Trial registration:**

Australian and New Zealand Clinical Trials Registry ACTRN12614000435684.

## Background

It has been estimated that globally, the percentage of the adult population with an active headache disorder is 46% for headache in general, 11% for migraine, 42% for tension-type headache, and 3% for chronic daily headache [1]. In the World Health Organization (WHO) ranking of causes of disability, headache disorders are in the 10 most disabling conditions for both genders, and the 5 most disabling conditions for women. Migraine has been ranked among the diseases causing the greatest degree of handicap, together with conditions such as quadriplegia, dementia and active psychosis [2].

A recent large study of the triggers of migraine attacks found 76% of migraineurs reported triggers when asked, and this figure rose to 95% when individuals responded to a specific list of triggers [3]. The most common headache triggers are: (i) stress and negative emotions; (ii) sensory triggers (flicker, glare, eyestrain, noise, odours); (iii) hunger; (iv) lack of sleep or excess of sleep; (v) food (particularly chocolate, cheese) and drink; (vi) alcohol; (vii) menstruation; and (viii) weather (cold, heat, high humidity) [4-6]. Many other factors have been noted including exercise, fatigue, sexual activity, and head and neck movement. A number of studies have investigated whether migraine and tension-type headache have the same or different triggers, and most have failed to find differences [7-9]. Some more recent studies have found differences with light, odours, hunger, weather and smoke being reported more commonly in migraine than tension-type headache, and head and neck movement being more common in tension-type headache [10,11].

Advice to identify and avoid triggers as a good means of preventing headaches, has been standard practice for decades. Researchers regularly make this point, for example, “comprehensive migraine treatment programs emphasize awareness and avoidance of trigger factors as part of the therapeutic regimen” [12]. One of the ‘seven elements of good headache management’ listed by WHO is “identification of predisposing and/or trigger factors and their avoidance through appropriate lifestyle change” [13]. This advice appears on numerous internet sites. For example, the American Headache Society website includes a handout entitled ‘Trigger Avoidance Information’. Headache Apps are now available for iPhones and iPads that encourage trigger avoidance (e.g., *iManage Migraine*, Merck & Co).

We have published three recent reviews arguing against counselling avoidance of all headache triggers [14-16]. It is not possible to completely avoid all potential headache triggers as they are so diverse; and attempting to do so could result in a restricted lifestyle [3]. It has been pointed out that the effort to avoid every potential headache trigger may itself be stressful [17]. Furthermore, advice to avoid triggers may lead to reduced internal locus of control for headaches, with attendant adverse effects on self-efficacy, particularly concerning perceived capacity to cope effectively with triggers [18].

In the chronic pain literature, fear-avoidance models have been developed, which contend that individuals who confront their pain are considered more likely to adaptively resume physical and social activities, whereas those who respond to pain with anxiety and avoidance are considered more likely to enter a self-perpetuating vicious cycle that maintains and exacerbates pain perception, leading to chronic pain and related disability [19]. In the stress literature, it has been argued that research findings indicate that coping with stress generally takes one of two routes, avoidance or approach, and the evidence demonstrates that the avoidance coping pathway is not adaptive, with a few important exceptions [20]. It has also been argued that higher levels of ‘experiential avoidance’, a type of avoidant coping, are associated with higher levels of general psychopathology and a lower quality of life [21].

The anxiety literature has demonstrated that short exposure to anxiety-provoking stimuli results in increased subsequent anxiety responses to the stimuli, whilst prolonged exposure results in decreased subsequent anxiety responses [22]. It is short exposure, resulting from attempts to avoid, or escape from, anxiety-eliciting situations, that underlies the maintenance of fears and phobias. In contrast, exposure-based approaches have been used with great success to treat a wide range of anxiety disorders [23]. A unified treatment approach for emotional disorders which includes preventing emotional avoidance (including behavioural avoidance and cognitive avoidance) and facilitating emotional exposure has been proposed [24].

A series of studies has investigated the relationship between length of exposure to various headache triggers and the capacity of the trigger to elicit head pain. In participants exposed to the experimentally-validated trigger of ‘visual disturbance’ [25] for one of five durations (‘none’, ‘very short’, ‘short’, ‘long’ and ‘very long’), nociceptive response was greater for the ‘short’ exposure condition than the ‘none’ and ‘very short’ exposure conditions; but the nociceptive response in the ‘very long’ condition was less than in the ‘short’ condition [26]. In summary, the results were consistent with the anxiety literature in that short exposure increased nociceptive response whereas very long exposure decreased nociceptive response. The study was repeated for the validated headache triggers of noise [27] and stress [28] with similar results. In a study in which migraine and tension-type headache sufferers attended the laboratory for six sessions of exposure to visual disturbance, ratings of visual disturbance, negative affect and headache intensity in response to the trigger, decreased from baseline by 44%, 54% and 63%, respectively, demonstrating desensitisation [29].

The arguments against advising avoidance of all headache triggers, and the findings linking prolonged exposure to decreased trigger potency, have led to us developing an alternative approach to trigger management called *Learning to Cope with Triggers* (LCT). The word ‘cope’ is used because of the insights that can be derived from the stress literature which demonstrate that no single coping strategy can be selected as the best way of coping with stress for all situations and across time, but reviewers have concluded that approach strategies generally are more adaptive than avoidance strategies [30]. We have argued that similarly, no one strategy can be singled out as the best way of managing all headache triggers. Sometimes avoidance will be the strategy of choice but more often, approach/engagement/exposure strategies will be more effective.

Following publication of three reviews advocating the LCT approach to trigger management, advice in the literature is now changing [31-33]. For example, the European Federation of Neurological Societies guidelines on the treatment of tension-type headache include “Identification of trigger factors should be performed, as coping with trigger factors may be of value” [31].

We recently published a study designed to evaluate the traditional advice to headache sufferers to avoid all triggers (‘Avoidance’) on the one hand, and LCT that included graduated exposure to selected triggers to promote desensitisation on the other hand [34]. Individuals (84 female, 43 male) with migraine and/or tension-type headache were assigned randomly to one of four groups: Waiting-list (Waitlist); Avoidance; Avoidance combined with CBT (Avoid + CBT); and LCT. Changes in headaches and medication consumption (in parentheses) from pre- to post-treatment were (a minus sign indicates improvement): Waitlist, +11.0% (+15.4%); Avoidance, −13.2% (−9.0%); Avoid + CBT, −30.0% (−19.4%); and LCT, −35.9% (−27.9%). Avoidance did not statistically differ significantly from Waitlist on headaches or medication use, but LCT differed significantly from Waitlist on both measures. Avoid + CBT significantly differed from Waitlist on headaches but not medication consumption. In summary, the study failed to find support for the traditional approach to trigger management of advising avoidance, but LCT emerged as a promising strategy.

Trigger management is only one aspect of a comprehensive approach to the treatment of headaches. Behavioural interventions have been shown to be quite efficacious for the treatment of headaches. A summary of meta-analytic reviews for behavioural treatment of migraine (thermal biofeedback, electromyographic - EMG - biofeedback, CBT, relaxation training) and tension-type headache (EMG biofeedback, CBT, relaxation training) concluded that average improvement ranged from 33% to 55%, compared with 5% for no-treatment controls for migraine, and from 35% to 55%, compared with 2% for no-treatment controls for tension-type headache [35]. We evaluated our version of CBT for migraine and tension-type headache in a randomised controlled trial and found no differences as a function of diagnosis [36]. CBT was associated with the following changes: (i) average decrease in headaches of 68% post-treatment, and 77% at 12-month follow-up; and (ii) average decrease in medication of 70% post-treatment. The average decrease in headaches at post-treatment of 68% (95% CI, 46.44 – 89.56) compares with the range of 33% to 55% from the review [35].

This study will integrate LCT into our version of CBT (LCT/CBT), and evaluate the efficacy of this new approach in anticipation of enhancing the effectiveness of CBT. LCT/CBT will be compared with CBT combined with the standard approach to trigger management of avoidance (Avoid/CBT), and with Waiting-list control (WL). The study will test the following hypotheses:LCT/CBT will result in greater decreases on the primary outcome measures of headaches, medication consumption and headache disability, than Avoid/CBT and WL.LCT/CBT will result in greater increases on the secondary outcome measures of self-efficacy, internal locus of control, and quality of life (less restricted lifestyle), than Avoid/CBT and WL.

The study will also investigate predictors of response to treatment and explore client-treatment matching hypotheses, such as whether participants who have a small number of triggers all of which are avoidable, would respond better to Avoid/CBT than LCT/CBT, whilst the reverse would be the case for participants who have more or less avoidable triggers. The response of migraine versus tension-type headache will be investigated, but there are no specific predictions related to diagnosis as the triggers of the two types of headaches are similar although not identical [10,11].

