#### Headaches, triggers and medication

For several decades, headache diaries have been recorded using paper-and-pencil, but such diaries have several important limitations including high researcher effort and error in data entry, high percentage of participant non-compliance, and inaccurately completed and missing items [43,44]. We have developed an e-diary using mobile software technology that can be used on a wide range of smartphone operating systems or installed on Windows computers. Research has shown that computerised pain diaries overcome several limitations of paper diaries [45], and recording exact time and date of diary completion significantly increases compliance rates [46,47]. In accordance with recommendations on the need to reduce client burden, the e-diary only includes seven items, which are widely considered as core questions to include in behavioural headache research [48]. The items are: current headache intensity; peak intensity; average intensity; number of headaches; average duration of headaches; medication consumption (number of pills taken); and headache triggers (checklist of 26 triggers). Participants are required to complete the e-diaries each day just prior to going to sleep, and a paper version is available for those who cannot use the e-diary system.

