### Statistical analyses and power considerations

The study design will focus on the interaction test of a mixed factorial design. Data will be tested for assumptions underlying both univariate and multivariate parametric analysis.

The power analysis is based primarily on the effect sizes generated in previous clinical trials of *f* = 0.33 to 0.42. Based on previous results an effect size of *f* = 0.25 (commonly accepted convention for a medium effect) can be confidently predicted. Power analysis using G*Power 3.1 software package indicates that for a three-group mixed factorial design with 40 participants per group and alpha = .05, moderate effects (*f* = .25) would be reliably identified with power .93 and a large effect (*f* = 0.4) would have an almost certain probability of being reliably identified.

Any missing data will be considered on an intention-to-treat basis [56,57] and fully analysed for the presence of Missing At Random, Missing Completely At Random, and Not Missing At Random patterns [58]. If statistically appropriate, missing data will be imputed using case-level multiple imputation. Data will be tested for assumptions underlying both univariate and multivariate parametric analysis. In addition to exploratory descriptive and correlational analyses, group by phase factorial ANOVAs using a Linear Mixed Models approach will be the main method of analysis for assessing treatment outcome. These will be supplemented by analyses of simple main effects and trend analysis (i.e., analysis of orthogonal polynomials) to examine the pattern of change over time for the experimental groups.

A linear mixed modelling approach has been chosen in order to permit: flexible structuring of the repeated covariance associated with the phase effect; more options for dealing with missing values; the analysis of individual change via growth curves; and options for analysing multi-level models, should they be theoretically or clinically relevant. For all inferential tests, measures of effect size (i.e., either *d* or η^2^) will be calculated, including confidence intervals around those measures. A range of clinical significance measures will also be considered [59]. Finally, regression analyses will be used to examine predictors of response to treatment, and moderation analysis will be used to examine the client-treatment matching hypotheses [60].

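### Hypothesis 1 has three unranked primary outcomes and no success rule, but the stated alpha of .05 and power of .93 belong to a single group-by-time test

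*Protocol article*

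**What the plan says.** The hypotheses in the Background section of the protocol article name three primary outcomes and two comparators together: "LCT/CBT will result in greater decreases on the primary outcome measures of headaches, medication consumption and headache disability, than Avoid/CBT and WL". No outcome is placed first, and no rule says how a mixed result would be read.

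The section on statistical analyses and power considerations puts the weight on one kind of test: "The study design will focus on the interaction test of a mixed factorial design". It adds that "group by phase factorial ANOVAs using a Linear Mixed Models approach will be the main method of analysis for assessing treatment outcome", with simple main effects and trend analyses as supplements. The only error rate appears in the power statement: "40 participants per group and alpha = .05, moderate effects (*f* = .25) would be reliably identified with power .93". That statement concerns one three-group test on one outcome. The article says nothing on multiplicity.

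**The concern.** A power statement and an error rate describe a hypothesis only once it is clear what counts as confirming it. Here one test is powered, while the hypothesis covers three outcomes.

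- If any one significant outcome is enough, there are three chances of a false positive at .05.
- If all three are needed, error is not inflated, but the chance of confirming a true Hypothesis 1 is below the .93 shown.

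A mixed result is realistic. In the authors' previous trial, described in the Background, Avoid + CBT differed from the waiting list on headaches but not on medication consumption. The Discussion makes later effectiveness research depend on results turning out as predicted, and the article does not say what that means when the three outcomes disagree.

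**Working it through.** **Inputs from the article.** Three primary outcomes, two comparators, 40 per group (N = 120, k = 3 groups), alpha .05, f = .25, stated power .93. **Assumed:** the correlation between outcomes, which the article does not give, varied from 0 to .9.

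**1. The plan's own figure.** I used the noncentral F for a group-by-time interaction, with λ = N·f²·m/(1 − r) and degrees of freedom (k − 1)(m − 1) and (N − k)(m − 1). With m = 2 time points and r = 0, λ = 120 × .0625 × 2 = 15 with df 2 and 117, and power is .938. This reproduces .93 to within a point. The article states neither m nor r, so these inputs are inferred. The calculation covers one outcome.

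**2. Any one outcome suffices.** For three independent interaction tests, family-wise error = 1 − .95³ = .143. For correlated outcomes I simulated 400,000 trials with no true effects, equal arms and normal statistics.

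**3. All three must succeed.** With independent outcomes and power .93 each, joint power = .93³ = .804. For correlated outcomes I integrated the equicorrelated normal probability that all three tests succeed.

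| Outcome correlation | Any of three interaction tests | Any of six ungated contrasts, either direction | Six contrasts, favouring LCT/CBT only | Joint power, all three at .93 |
|---|---|---|---|---|
| 0 | .14 | .25 | .13 | .80 |
| .3 | .14 | .24 | .12 | .82 |
| .5 | .13 | .22 | .11 | .84 |
| .7 | .11 | .19 | .10 | .86 |
| .9 | .09 | .15 | .07 | .89 |

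The six-contrast columns allow for the shared LCT/CBT arm. They are there for comparison, because the article does not describe that analysis.

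**4. Splitting alpha.** With Bonferroni over three outcomes (.05/3 = .0167) and the inputs of step 1, power falls from .938 to .864. An adjustment of this kind therefore also changes the power figure.

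**5. Checking the remedy.** Suppose both CBT arms beat the waiting list but do not differ from each other. The waiting list alone can then make every interaction test significant. If only the interaction test governs the move to the next outcome, the LCT/CBT versus Avoid/CBT contrast is false-positive somewhere with probability about .08 to .14 (correlation .9 to 0). If that contrast must also be significant before moving on, the probability is .05.

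**The case against.** The strongest reply is that this is silence in a condensed article. Multiplicity rules commonly sit in a full protocol or analysis plan, the trial is Phase II, and the article never says that .93 is the power of Hypothesis 1 as a whole. Hypothesis 1 is also worded with *and* throughout, so it can be read as requiring every outcome against both comparators. On that reading the false-positive risk is below .002.

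Much of this stands. No adjustment can be called absent on this evidence, and the conjunctive reading removes the inflation.

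A reader might also infer that six comparisons are each run at .05, so that the risk of a false success is about four times nominal. The article does not support this. It makes the interaction test the focus and nowhere says that six contrasts are tested separately. The fourfold figure needs six two-sided contrasts with no gate, counted in either direction, any one sufficient, and an outcome correlation of about .5 to .7. Hypothesis 1 is directional, and counting only results that favour LCT/CBT gives .07 to .13 even across six contrasts.

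Nor does it belong to this point that several diary items could be used to score headaches. That is outcome derivation, which an analysis plan may settle.

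What the reply does not remove is the mismatch in the printed text. Splitting alpha lowers the power, leaving alpha whole inflates the error if any outcome counts, and requiring all three lowers the joint power. A fixed order keeps .93, but for the first outcome only. Under each of these rules the power statement needs to say what it covers.

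**Conclusion.** The point holds in a limited form. Three unranked primary outcomes share one alpha and one power figure that were worked out for a single interaction test.

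- **Any outcome counts:** family-wise error is about .09 to .14, or 1.7 to 2.9 times .05. This assumes no true effects and an outcome correlation from .9 down to 0.
- **All three must succeed:** joint power is about .80 to .89 over the same correlations, taking .93 as the power of each test.

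The range of .15 to .25 would apply only to six ungated two-sided contrasts, which the article does not describe. An unseen analysis plan may already fix the success rule, but it could not make .93 the power of the whole hypothesis unless the outcomes were all but perfectly correlated. The point should be corrected. It does not threaten the design.

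**What to change.** Add two or three sentences to the section on statistical analyses and power considerations:

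- The primary outcomes are tested in the order in which Hypothesis 1 lists them: headaches, then medication consumption, then HDI. Each is tested at two-sided .05, and confirmatory testing stops at the first non-significant result.
- Within each outcome, LCT/CBT versus Avoid/CBT is the key comparison and the waiting-list contrast is supportive. Testing moves to the next outcome only if both the interaction test and the key comparison are significant (step 5 of the working shows why).
- The power of .93 refers to the interaction test on headaches only.

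The interaction test on headaches keeps its full alpha and its stated power, and the sample size does not change. The cost is that medication consumption and HDI cannot be claimed as confirmatory if headaches is not significant. The listing order also becomes a real hierarchy, so the investigators should confirm that it is the one they want. If an analysis plan already sets another rule, state that rule here and match the power sentence to it.
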